## **9.2 Pre-study Task**

Before the first patient is enrolled, the sponsor's representative will visit the study center to:

1. Confirm whether the study center's facilities are adequate;
2. Confirm whether there are suitable patients to be enrolled in the study center;
3. Discuss with investigators (and other study-related personnel) their responsibilities for the protocol and the responsibilities of the sponsor or its representative.

## **9.3 Training of Study Center Personnel**

Before the first patient is enrolled in the study, the undertaking unit will provide standardized trainings and examinations to the principal investigator and all other investigators of the sub-center, and the study will only be started in the sub-center once the examinations are passed. The principal investigator will make sure that all study-related personnel are trained properly for the study with complete training records.

## **9.4 Study Monitoring**

During the study, the sponsor will contact the study centers regularly, including:

1. Visits to provide information and support to the investigators;
2. Confirm that the facility still meets the requirements;
3. Confirm whether all study-related personnel follow the protocol, the data is recorded in the CRF promptly and accurately, and numbers of the IMPs are checked;
4. Compare the data in the CRF with the records of the patients generated in the study centers, including the inspection on ICF of the patient. All original records of each patient will be directly examined.

Investigators will contact the sponsor during the follow-up intervals for information and recommendations related to the study.

## **9.5 Source Data**

The undertaking unit will store all original records and source data, which will be inspected and reviewed by the CFDA (now NMPA).

## **9.6 Study Progress**

If the procedures at a study center are not conducted in accordance with Good Clinical Practice (GCP) requirements, or if the recruitment period is too long, the study at that center may be terminated. The study sponsor may terminate the study early due to safety concerns about the study.

# **10. AEs**

Any information on AEs, whether mentioned by patients and found by investigators, or detected in physical examinations, laboratory tests, or by other means, will be recorded in the AE pages of the CRF, and these AEs will be treated and reported pursuant to related laws.

## **10.1 Definition of AEs**

Any adverse medical events, or worsening of pre-existing medical events from the start of the randomization

to the last visit, whether or not causally related to the IMPs, are regarded as AEs. During the clinical study, any unexpected events that happen to the patients will be defined as AEs. Adverse medical events include clinical symptoms (such as nausea and chest pain), signs (such as tachycardia and hepatomegaly), and abnormal test results (including laboratory tests and ECG). The physicians will report all AEs directly observed by themselves or spontaneously reported by the patients concisely with medical terminology. Adverse drug reactions are the reactions that are directly or indirectly related to drugs. To prevent any omission of adverse drug reactions when the relationship between an AE and drugs can hardly be determined, all AEs will be recorded in the CRF, including occurrence time, severity, duration, treatment measures, and outcome. Additionally, all relationships between AE and drugs will each be stated.

## **10.2 Observation and Records of AEs**

All patients who have received at least 1 dose of the IMPs will undergo a safety evaluation with the following events recorded: AEs, SAEs, deaths, recurrent strokes, drug discontinuation for any reasons, abnormal laboratory test results, vital sign changes, and changes to physical examination results. Any AE that happens from the start of the randomization to 12 months after the enrollment or the last visit will be recorded. A patient with an AE will be followed up until the event disappears, restored to the baseline level, or becomes clinically insignificant. All AEs occurring during the study will be recorded in the CRF. The evaluation will include the name of AE, severity, outcome, relationship between AEs and IMPs, and treatment measures.

## **10.3 Severity of AEs**

1. Mild: mild symptoms or diseases that improve rapidly after drug discontinuation and require no treatment;
2. Moderate: transient damages that do not require hospitalization or prolonged hospitalization but do require treatment or interventions, and can be easily relieved;
3. Severe: transient damages that require an out-patient to be hospitalized or an in-patient to prolong the hospitalization by more than 7 days, or permanent damages to systems/organs, or life-threatening events (asphyxia, shock, coma, and other symptoms that require first aid treatment).

## **10.4 Correlation between the AE and Drugs**

Investigators will evaluate the correlation between AEs and the IMPs as well as concomitant medications:

1. Definitely related: the onset time follows the time sequence after administration, and the AE is consistent with a known type of adverse reactions of the suspected drug; the adverse reaction improves or disappears after the dose reduction or drug discontinuation but reappears after resuming the drug administration;
2. Probably related: the onset time follows the time sequence after administration, and the AE is consistent with a known type of adverse reactions of the suspected drug; the adverse reaction improves or disappears after the dose reduction or drug discontinuation but it may also be caused by the clinical status of the patient or other reasons;
3. Possibly related: the onset time follows the time sequence after administration, and the AE is consistent with a known type of adverse reactions of the suspected drug; the adverse reaction improves or disappears after the dose reduction or drug discontinuation but it can be explained by the clinical status of the patient or other reasons;
4. Unlikely related: the onset time is unlikely to follow the time sequence after administration, and the AE is hardly consistent with a known type of adverse reactions of the suspected drug; the adverse reaction is possibly caused by the clinical status of the patient or other reasons;
5. Definitely unrelated: the onset time does not follow the time sequence after administration, and the AE is hardly consistent with a known type of adverse reactions of the suspected drug; the reaction can be explained by the clinical status or other reasons of the patient and it improves or disappears after removing the clinical status or other reasons;
6. Unknown.

Summarize the AEs of the first three criteria in each CRF and calculate the incidence of drug-related AEs.

619       **10.5 SAEs**

620       SAEs are defined as the AEs leading to following results:

- 621       1.   Death;
- 622       2.   Life-threatening (the AE occurrence leads to a life-threatening risk to the patient, excluding the AEs that  
623       are assumed to be potential causes of deaths if worsened) event;
- 624       3.   Hospitalization or prolonged hospital stay;
- 625       4.   Continuous or significant disability/dysfunction;
- 626       5.   Congenital malformations or birth defects;
- 627       6.   Medical events considered as SAEs by the investigator.

628       In case of a SAE during the trial, whether related to the IMPs or not, the investigator will immediately take  
629       treatment measures for the patient for their safety and will report it to the CRA, the ethics committee of the  
630       center, and the undertaking unit within the 24 h after it occurs. The undertaking unit will report it to ethics  
631       committees and the sponsor, as well as the CFDA (now NMPA) for filing. The investigator will complete the  
632       filling of the SAE form.

633       In case of a SAE that has not been resolved after the end of the trial or the early withdrawal of the patient will  
634       be followed up until any of the following circumstances:

- 635       1.   Event disappears or is resolved;
- 636       2.   Stable event;
- 637       3.   Event is restored to baseline;
- 638       4.   Event is relieved to be clinically insignificant;
- 639       5.   Event can be attributed to the drugs other than the IMPs or factors unrelated to the study, or that any more  
640       information is unlikely to be obtained (the patients or medical staff refuse to provide more information, or  
641       there is evidence that the patient is still lost to follow-up despite best efforts).

642       **10.6 Record, Management, and Report**

- 643       •   Any AEs during the trial, whether related to the IMPs or not, will be documented;
- 644       •   AEs related to IMPs will be managed carefully;
- 645       •   Patients will be required to report any changes after the drug administration;
- 646       •   Investigators will avoid asking inductive questions. While observing the efficacy, the patient will be  
647       closely monitored for AEs and unexpected toxic or side effects (including symptoms, signs, and laboratory  
648       test results), which will be analyzed for reasons, judged, followed up, and recorded;
- 649       •   Incidence of AEs will be calculated;
- 650       •   Symptoms, severity, occurrence time, duration, treatment measures, outcomes, correlation to drugs, and  
651       follow-up modes of the AEs during the trial will be recorded in CRF in detail, and the CRF will be signed  
652       and dated;
- 653       •   When an AE is found, investigator may decide whether to discontinue the study according to the patient's  
654       condition, and will carry out a follow-up investigation on the case of drug discontinuation due to AEs and  
655       record the process and results in detail;
- 656       •   In case of any SAE or important AE occurring during the study, the investigator will initiate emergency  
657       procedures;

- Among all patients who have received the study treatment, those experiencing AEs will be included in AE statistics, regardless of whether they have completed the whole trial.

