### 219 **4.4 Secondary Safety Outcomes**

- 220 1. Incidence of symptomatic intracranial hemorrhage within 3 months of treatment;
- 221 2. Incidence of all-cause mortality within 3 months of treatment;
- 222 3. Incidence of AEs within 3 months of treatment.

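### Section 10.4 admits an adverse event to the drug-related count only if it is of a known type and improves on dose reduction or stopping, which biases the drug-related AE incidence downward

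*Protocol*

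**What the plan says.** Section 10.4 gives investigators six causality categories. The first three are the related ones.

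- *Definitely related*: "Definitely related: the onset time follows the time sequence after administration, and the AE is consistent with a known type of adverse reactions". In addition, "the adverse reaction improves or disappears after the dose reduction or drug discontinuation but reappears after resuming the drug administration".
- *Probably related*: "Probably related: the onset time follows the time sequence after administration, and the AE is consistent with a known type of adverse reactions". In addition, "the adverse reaction improves or disappears after the dose reduction or drug discontinuation but it may also be caused by the clinical status".
- *Possibly related*: "Possibly related: the onset time follows the time sequence after administration, and the AE is consistent with a known type of adverse reactions". In addition, "the adverse reaction improves or disappears after the dose reduction or drug discontinuation but it can be explained by the clinical status".

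*Unlikely related* and *definitely unrelated* describe an onset that probably does not, or does not, fit the timing of administration, together with poor agreement with known reactions and another explanation. The sixth category is *Unknown* and has no definition.

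The section closes with the counting rule: "Summarize the AEs of the first three criteria in each CRF and calculate the incidence of drug-related AEs".

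Other sections bear on this. Section 10.1 defines an adverse drug reaction as any reaction linked to the drug directly or indirectly, and has every AE recorded so that reactions of uncertain cause are not missed. Section 10.3 places permanent organ damage and life-threatening events in the severe grade. Section 10.5 lists death and lasting disability among SAEs. Section 10.6 asks investigators to watch for, analyse and judge unexpected toxic effects.

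**The concern.** A causality scale normally loosens its conditions as certainty falls. This one does not: a known reaction type and improvement after reduction or stopping are required at every related level. Only the recurrence condition and the strength of the alternative explanation change from one level to the next.

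The events that fail these conditions include ones a safety review most wants to see attributed: reactions not described before, reactions that end in death, and reactions that do not reverse. If the scale is applied as worded, the drug-related AE incidence looks more favourable than the investigators' own suspicion would support. The loss arises when the category is entered in the CRF. A later analysis could display the *Unknown* group, but it could not recover a judgement that the definitions did not allow.

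**Working it through.** No rate or sample size enters this point, so the check is logical. Each category is read as the conjunction of its stated conditions.

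| Category in 10.4 | Timing | Known reaction type | Improves after reduction or stopping | Counted as drug-related |
|---|---|---|---|---|
| 1 Definitely | plausible | required | required, plus recurrence on resuming | yes |
| 2 Probably | plausible | required | required | yes |
| 3 Possibly | plausible | required | required | yes |
| 4 Unlikely | improbable | hardly consistent | not stated | no |
| 5 Definitely unrelated | absent | hardly consistent | not stated for the drug | no |
| 6 Unknown | none | none | none | no |

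Now take events whose onset does fit the timing of administration. Categories 4 and 5 are closed to all of them by the timing condition.

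| Plausibly timed event | Condition failed in categories 1 to 3 | Only category left | Counted |
|---|---|---|---|
| Known type, improves after reduction or stopping | none | 1, 2 or 3 | yes |
| Known type, fatal or no improvement | improvement, in 3 of 3 | Unknown | no |
| Known type, drug neither reduced nor stopped | improvement after reduction or stopping, in 3 of 3 | Unknown | no |
| New type, improves | known type, in 3 of 3 | Unknown | no |
| New type, no improvement | both, in 3 of 3 | Unknown | no |

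Only the first row reaches the drug-related incidence. Permanent damage of a known type that partly improves can also reach it, because improvement need not be complete.

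Let *n* be the patients with an event in categories 1 to 3, *u* the further patients whose only truly related events fall in the four excluded rows, and *N* the patients treated. The rule reports *n/N* where *(n + u)/N* is wanted, so the share missed is *u/(n + u)*. The protocol gives neither *n* nor *u*. The share is zero if no such event occurs and rises with *u*, and no single value can be defended.

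Set beside the other sections, 10.4 does not fit. Section 10.1 puts no condition of known type or reversibility on an adverse drug reaction, and section 10.6 requires unexpected effects to be judged. Yet 10.4 has no related category in which an unexpected effect can be placed.

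**The case against.** The strongest reply is that little depends on this scale, and much of that reply stands.

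- A reader might infer that the hemorrhage and mortality outcomes are undercounted. They are not. Section 4.4 sets "Incidence of symptomatic intracranial hemorrhage within 3 months of treatment" and all-cause mortality without any relatedness condition. The third outcome there is all AEs, and the primary safety outcome in 4.3 is all SAEs. None of the four uses 10.4. The safety analysis in 13.2.3 pools AEs and SAEs by group and describes all deaths and SAEs in narratives, without mention of relatedness.
- A reader might infer that the categories drive decisions on treatment. Sections 7.6.1 and 7.6.2 speak of relatedness but rest on the investigator's judgement and do not cite the 10.4 categories. SAEs are reported within 24 h whatever the cause (10.5), and the DSMB reviews AE incidence and safety outcomes regularly (8.4.1).
- A reader might say that no irreversible or serious reaction can ever be counted, or that the undercount is total. That is too strong. Partial improvement meets the wording, a non-fatal hemorrhage can improve, and investigators may not apply the scale to the letter.
- A reader might treat the reactions listed in section 1 as the closed set of known types, so that bleeding is excluded. Section 1 describes what was mostly reported, and 10.4 does not refer to it. The same section says that a component of the product inhibits platelet aggregation. The protocol does not settle whether bleeding is a known type.

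These points narrow the reach. They do not answer the defect: the definitions leave no related category for the excluded events, and the counting rule then drops them.

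**Conclusion.** The point holds as a defect of definition in 10.4. As worded, the drug-related AE incidence omits plausibly timed events that are new in type, fatal, not improving, or that occur without any reduction or stopping of the drug. It is biased downward by an amount that the protocol does not allow one to calculate. Section 10.4 also conflicts with 10.1 and 10.6.

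The effect is confined to causality attribution and to that one descriptive incidence. The conclusion assumes that investigators apply the categories literally and that *Unknown* stays outside the count, as the closing sentence of 10.4 implies. It should be corrected, but it does not threaten the trial's stated safety outcomes.

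**What to change.** In 10.4 and in the CRF completion guidance:

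1. Redefine *possibly related* as plausible timing with a causal role of the drug that cannot be excluded. Require neither a known reaction type nor improvement after stopping.
2. Where improvement cannot be observed, because the event is fatal or irreversible or the drug was neither reduced nor stopped, record it as not assessable and state that this does not lower the category.
3. Let categories 4 and 5 also take plausibly timed events with a clear non-drug cause. Otherwise such events have nowhere to go but *Unknown*.
4. Report *Unknown* separately by group beside the drug-related incidence, with an optional sensitivity figure that includes it. Do not merge it into the main figure: with categories 4 and 5 as they stand, *Unknown* also collects plausibly timed events of evident non-drug cause, and merging would inflate the rate.

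The cost is a wording change in the protocol and CRF guidance and a short note in investigator training. Sample size, visits and data items for the safety outcomes are unaffected. The drawback is that the reported drug-related AE rate may become less favourable.

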## **10.7 Emergency Procedures**

In case of any SAE or important AE occurring during the study, the investigator will immediately organize a rescue for the patient to ensure his/her safety. The undertaking unit will be informed of the event immediately via telephone/fax, to clarify whether or not the event is IMP related or if the IMP has been administered. Subsequently, the CRA will provide a written report to describe the details and outcome of the event. In addition to confirmation of the content reported by telephone/fax, the written report will also contain other unmentioned information. The CRA will check the written report and report to the drug safety department according to GCP standard operating procedures within 24 h or no later than the second working day after receiving the phone call.

## **11. Ethical and Regulatory Requirements**

### **11.1 Independent Ethics Committee Approval**

According to the local regulations, all protocols (and relevant amendments, if any), including patient information and informed consent, will obtain the approval of independent ethics committee before implementation. The reports related to the progress of trial, including notification of matters regarding the completion or termination of trial, will be submitted to the independent ethics committee by the investigator or sponsor.

### **11.2 Patient Information and Informed Consent**

These documents will be created according to International Conference on Harmonization-Good Clinical Practice guidelines, and will be provided to the independent ethics committee as separate documents. Only approved versions will be used for the trial. During the process to obtain and record informed consent, the investigator will comply with relevant local regulatory requirements and the Declaration of Helsinki. Prior to initiation of activities related to the study, investigator will verbally describe the information on this study to the patients, and provide relevant written information that is readable and understandable for the patients. The ICFs signed and dated voluntarily by each patient will be obtained. The written ICF will be signed and dated by the personnel who is responsible for the implementation of informed consent procedures. The patients enrolled in the study will be informed that they can refuse to participate in the study and their medical care will not be affected. Information on their medical conditions will be collected and recorded, and all findings will be handled in strict confidence. Patients will be provided with the copies of patient information and ICF.

### **11.3 Essential Documents**

1. Latest curriculum vitae of the principal investigator;
2. Investigator signature page in the protocol;
3. Copies of dated documents related to the protocol and local investigators that have been approved by the independent ethics committee, including any amendments, patient information and ICF, compensation (if any), and any other documents that have been submitted;
4. Contracts signed between the sponsor and the study centers;
5. Approval documents from the local hospital management authority if necessary;
6. Other relevant documents that are required before the initiation of study.

## **12. Data Management**

### **12.1 Data Acquisition and CRF**

CRFs will be filled in by the investigator and will be completed for each enrolled patient. An electronic data

capture system will be used for data acquisition for all CRFs. All data will be reviewed and submitted by the CRA to the data administrator for data management.

## **12.2 Data Management Procedures and Tasks**

### **12.2.1 Design of CRF and Database**

The design of CRF will ensure that the collection of all data meets the requirements for statistical analysis as specified in the protocol. Guidelines for completing the corresponding CRFs will be established. Logical verification will be established according to the design description of database, and the database will be put into use after passing the user acceptance testing.

### **12.2.2 Receipt of Data**

Data collection and management of this study will follow the requirements of GCP. The data administrator designated by the statistics agency will be responsible for data acquisition and management. The data administrator will compile a program for data acquisition and management. The clinical investigator or clinical research coordinator will fill in the CRFs in an accurate, timely, complete, and standardized manner according to the CRF guidance. Instructions for data acquisition will be formulated before data acquisition to determine relevant requirements and methods. For any question about the CRF, the data administrator will create a data rating questionnaire, and send a query to the investigator through the CRA. The investigator will give a reply as soon as possible, and the data administrator will modify and confirm the data according to the investigator's reply, or send another questionnaire when necessary.

